### Adverse events

We define adverse events as unfavourable or unintended signs, symptoms or disease occurring after treatment that are not necessarily related to the acupuncture intervention. Acupuncture-related adverse events are defined as local symptoms including bruising and pain for over two weeks at acupuncture points, peripheral neuritis and swelling, redness and itching for over three days, systemic symptoms including dizziness and palpitation, and psychiatric problems including headache for over three days, anxiety or fear for over 60 hours, and hypersensitivity for over three days. In case of serious medical problems, other symptoms could be included in adverse events. In every visit, adverse events will be reported by participants and examined by the practitioner.

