### Study aims

This study aims to evaluate the effectiveness and safety of acupuncture treatment for dry eye. The null hypothesis of this study is "the change in dry eye symptoms after verum acupuncture treatment is equal to the change in dry eye symptoms after sham acupuncture treatment."

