### Sham acupuncture group (non-acupuncture point shallow penetration group)

A sham acupuncture point corresponding to each verum acupuncture point was selected. The principle of sham point selection is that the sham point should not be a classical acupuncture point and should, except for points on the rim of the eye, be located close to the verum point. The selected sham points are as follows: both points 2 cm lateral to ST4, 2 cm below ST7, at the parietal eminence of head, 2 cm internal to ST9, 10 cm internal to BL57, 1.5 cm internal to ST36, one point at the left middle point of the bicepsbrachii muscle belly, points at 2 cm, 4 cm, and 6 cm from the Lt. wrist fold, and one point located between the Lt. 3^rd ^and 4^th ^metatarsophalangeal joints. After shallow penetration of the skin at each site with no manipulation for 'de qi,' the needle is left for 20 minutes. Every participant in the sham acupuncture group will be treated three times per week for three weeks.

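### Bruising and pain count as acupuncture-related only at acupuncture points, a term that read literally excludes every sham needle site

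*Protocol article*

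**What the plan says.** Safety is one of the two stated aims (Study aims): "This study aims to evaluate the effectiveness and safety of acupuncture treatment for dry eye".

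The Adverse events section sets two levels. The general class is broad and applies to both arms: "unfavourable or unintended signs, symptoms or disease occurring after treatment that are not necessarily related to the acupuncture intervention". Within it, a related class is defined, starting with local symptoms: "Acupuncture-related adverse events are defined as local symptoms including bruising and pain for over two weeks at acupuncture points". The same sentence goes on with "peripheral neuritis and swelling, redness and itching for over three days", followed by systemic and psychiatric symptoms. Events are reported by participants at every visit and examined by the practitioner.

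The control arm is headed "Sham acupuncture group (non-acupuncture point shallow penetration group", and its sites follow a stated rule: "The principle of sham point selection is that the sham point should not be a classical acupuncture point". The same section also says "A sham acupuncture point corresponding to each verum acupuncture point was selected". The sham needles break the skin: "After shallow penetration of the skin at each site with no manipulation for 'de qi,' the needle is left for 20 minutes".

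**The concern.** A sham needle that penetrates the skin can bruise or hurt, as a verum needle can. If the label for such an event depends on whether the site is an acupuncture point, and the sham arm is built from sites that are not, then the same event can be classed differently according to arm.

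What is at stake is the meaning of a between-arm contrast. The sham arm is the only comparator, so it is what would separate harm specific to verum acupuncture from harm of needling in general. If related bruising and pain can be coded under verum only, an excess in that arm partly reflects the definition. The objection is to a criterion the article states, not to detail left to a fuller document.

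**Working it through.** The question is one of wording, and the article gives no figure to reproduce. The relevant texts are set side by side below.

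**1. Which symptoms carry the site condition?** The local symptoms in the Adverse events section are:

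| Local symptom | Tied to acupuncture points? |
|---|---|
| Bruising | Yes |
| Pain | Yes |
| Peripheral neuritis | No |
| Swelling | No |
| Redness | No |
| Itching | No |

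The site condition follows bruising and pain and comes before the comma that opens the remaining items. Two of six listed local symptoms are affected and four are not. The systemic and psychiatric items have no site at all.

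**2. Are sham sites acupuncture points?** By the selection rule and the group heading, they are not. The abstract describes the sham in the same way. In the Verum acupuncture group section, the term without a qualifier refers to the seventeen verum points. In the sham section, sites are marked with the word sham. The Adverse events section uses the unqualified term, so the literal reading is verum sites only.

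**3. Can the two symptoms arise in the sham arm?** Yes. The number of needle sites is the same in both arms:

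- Verum: 6 bilateral points × 2 = 12, plus 4 unilateral limb points, plus GV23, gives 12 + 4 + 1 = 17.
- Sham: 6 bilateral sites × 2 = 12, plus 1 on the arm muscle, 3 near the wrist and 1 on the foot, gives 12 + 1 + 3 + 1 = 17.

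Over nine sessions that is 17 × 9 = 153 insertions per participant who completes treatment, or 153 × 21 = 3,213 per arm if all 21 complete. These figures measure exposure. They are not counts of events or of misclassified events.

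**4. Who applies the term?** Under Sample size and randomisation, the acupuncture practitioners open the allocation. Under Adverse events, the practitioner examines the events. Taking this to be the treating practitioner, the person who decides whether a site is an acupuncture point knows the arm. The blinding of outcome assessors does not cover this step.

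**5. What happens to a sham-site bruise or pain on the literal reading?** It fails the site condition for the related class but meets the general definition. The event is kept and its label changes.

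**The case against.** The strongest reply has four parts.

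*The rule does not exclude all local harm in the sham arm.* This stands. A reader might infer that local needling harm is captured in the verum arm only, or that the sham arm's rate of related local events is zero by definition. The documents do not support either inference. Four of the six listed local symptoms have no site limit, and the list is introduced as non-exhaustive, so other sham-site events could be classed as related. That last route depends on discretion, however, and not on the stated criterion.

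*The literal reading is not the only one.* This stands in part. The protocol calls the sham sites sham acupuncture points, says that acupuncture is carried out in both groups, and bars only classical points from the sham. The term could therefore mean needled points in either arm. But that reading sits badly with an arm headed as non-acupuncture-point, and with the use of the unqualified term for verum points. The phrase makes the term ambiguous without curing it, because the two readings classify the same sham-arm event differently.

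*No event is lost.* This stands. Recording is the same in both arms at every visit.

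*No comparison of related events by arm is announced.* This is correct. The Statistical analysis section covers baseline, primary and secondary outcomes, and safety tables may be set out in a document not shown. That a comparison will be made is an inference from the safety aim and the two-arm design. A later safety table would normally take over the protocol's definition, so the wording still matters.

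**Conclusion.** The point holds in a limited form and is minor. For persistent bruising and persistent pain, the stated criterion for relatedness depends on arm when read literally, and is ambiguous at best. It is applied by someone who knows the allocation. A between-arm comparison of these two symptoms in the related class could therefore be partly an artefact of the definition.

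The size cannot be calculated, because the documents give no rate for bruising or pain lasting over two weeks. It is probably small: two of six listed local symptoms are involved, only persistent cases of them qualify, and only the label is at risk. The equal number of insertions should not be taken as a measure of bias.

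The conclusion rests on three assumptions: that the site condition and the duration apply to both bruising and pain; that the unqualified term is read as it is used for the verum points; and that related events will be looked at by group.

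**What to change.** In Adverse events, replace the words 'at acupuncture points' with 'at any needle insertion site, verum or sham'. State that the same needling-related definition applies to both arms, and use it when counts are tabulated by group. Make the same change on the adverse-event form.

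The cost is one phrase in the protocol and one on the form. Visits, treatment, staffing and sample size are unchanged.

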### Secondary outcome measurement

The visual analogue scale (VAS) for self-assessment of ocular discomfort will be used. Self-reports on ocular symptoms concomitant with dry eye will be obtained for such conditions as ocular itching, foreign body sensation, burning, pain and dryness as well as for blurred vision, sensation of photophobia, ocular redness and sensation of tearing. Each participant will record a score indicating his or her total level of discomfort on a 100 mm horizontal line.

Tear Film Break-Up Time (TFBUT) and the Schirmer I test with anaesthesia will be used as additional secondary outcome variables. TFBUT is a method for observing tear film stability. Sodium fluorescein (2.5%) will be instilled in both eyes and the tear break-up time (the interval between the last complete blink and the first appearance of a dry spot or disruption in the tear film) will be measured [18]. The Schirmer I test with anaesthesia is a method for checking basic tear secretion. Schirmer test paper (Color Bar™ Eagle Vision, USA) will be inserted on the lateral third of the lower eyelid with the participant's eye closed for five minutes. Each test will be performed by a single ophthalmologist.

Medication Quantification Scale (MQS) and General Assessment of Improvement will also be used as secondary outcome variables. The total frequency and dosage of artificial tears will be checked. At the final visit of each participant, both participant and practitioner will assess improvements in ocular symptoms. 'Excellent' indicates the presence of no symptoms related to dry eye and much improvement in daily life; 'Good' means that a few symptoms related to dry eye are present but that the condition is better than before treatment; 'Fair' means that several symptoms related to dry eye are present but that the condition is a little improved; 'Poor' means that there is no change compared with before treatment; 'Aggravation' means that symptoms are worse than they were before treatment (Table 1).

**Table 1 T1:** Schedule for treatment and outcome measurement

Period	screening										F/U
Visit	1	2	3	4	5	6	7	8	9	10	11
Week		1st			2nd			3rd			Visit10+ 1 week+ 3 days
Informed consent	ν										
Demographic characteristics	ν										
Medical History	ν										
Physical examination	ν										
Random Allocation		ν									
Acupuncture Treatment		ν	ν	ν	ν	ν	ν	ν	ν	ν	
Symptom score	ν	ν	ν	ν	ν	ν	ν	ν	ν	ν	ν
OSDI		ν		ν			ν			ν	ν
Schirmer I test	ν									ν	
TFBUT	ν									ν	

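### The acupuncture-related adverse event count depends on how long symptoms last, and its two-week item cannot be confirmed by visit 11 for the latest sessions

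*Protocol article*

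**What the plan says.** The Adverse events section has two layers. The first is general and sets no minimum duration: "We define adverse events as unfavourable or unintended signs, symptoms or disease occurring after treatment that are not necessarily related to the acupuncture intervention". Collection is repeated: "In every visit, adverse events will be reported by participants and examined by the practitioner". Table 1 marks a safety assessment at visits 2 to 11.

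The second layer defines the acupuncture-related category: "Acupuncture-related adverse events are defined as local symptoms including bruising and pain for over two weeks at acupuncture points". Further limits follow for other local symptoms ("swelling, redness and itching for over three days") and for psychiatric ones ("headache for over three days, anxiety or fear for over 60 hours, and hypersensitivity for over three days"). One group carries no limit: "systemic symptoms including dizziness and palpitation". Peripheral neuritis has none clearly attached.

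Table 1 times the last visit as "Visit10+ 1 week+ 3 days". The Study aims section gives safety equal standing with effect: "This study aims to evaluate the effectiveness and safety of acupuncture treatment for dry eye".

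**The concern.** Whether the needle caused a symptom and how long the symptom lasted are separate questions. For the symptoms with a limit, the definition makes the second decide the first. Needle-site pain that lasts 10 days is then not acupuncture-related, whatever its cause.

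This bears on the comparison between arms. Verum needles are twisted to obtain de qi, while sham needles penetrate shallowly without manipulation. Short-lived local pain and bruising are events on which the arms could plausibly differ, and the related category can leave them out. A low related count would then partly reflect the definition.

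The second difficulty is timing. A criterion of more than two weeks is paired with a last scheduled safety visit less than two weeks after the final session.

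**Working it through.** The plan gives no figure on this point to reproduce. The check is a comparison of definitions and a count of days.

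**Definitions side by side.** Take needle-site pain lasting 10 days. It meets the general definition, so it can be recorded. It fails the two-week limit, so it is not acupuncture-related. The same holds for a bruise if the limit covers bruising, but not if the limit qualifies pain alone. The sentence allows both readings.

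**Inputs for the day count**
- Limit: more than 14 days (Adverse events).
- Sessions: nine, three per week for three weeks (Verum acupuncture group; Sham acupuncture group), at visits 2 to 10 (Table 1).
- Visit 11 (Table 1): 7 + 3 = 10 days after visit 10 if taken literally, or 7 to 10 days if the three days are an allowance.
- Days of the week: not given. Monday/Wednesday/Friday is assumed first, then varied, with the same days each week.
- Onset: assumed on the session day. Later onset shortens observation further.

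**Formula.** Session i is on day s_i, and visit 11 is on day F = s_9 + k, with k = 7 or 10. A symptom from session i can be confirmed as lasting more than 14 days by visit 11 only if F − s_i > 14.

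**Monday/Wednesday/Friday**

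| Session | 1 | 2 | 3 | 4 | 5 | 6 | 7 | 8 | 9 |
|---|---|---|---|---|---|---|---|---|---|
| Day | 0 | 2 | 4 | 7 | 9 | 11 | 14 | 16 | 18 |
| Days observed, k = 10 (F = 28) | 28 | 26 | 24 | 21 | 19 | 17 | 14 | 12 | 10 |
| Days observed, k = 7 (F = 25) | 25 | 23 | 21 | 18 | 16 | 14 | 11 | 9 | 7 |

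- k = 10: sessions 7 to 9 do not exceed 14 days, so 3/9 = 33%.
- k = 7: sessions 6 to 9 do not exceed 14 days, so 4/9 = 44%.

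**Other calendars.** Let g be the days from a session to the third session of its week. Days observed are g + k in week 3, g + 7 + k in week 2 and g + 14 + k in week 1.
- k = 7: week 3 would need g > 7, which is impossible. Week 2 fails only at g = 0. The result is 4 of 9 on every calendar.
- k = 10: week 3 needs g of at least 5, and weeks 1 and 2 always pass. Weekday patterns have g of at most 4, so 3 of 9 fail. Monday/Thursday/Saturday (g = 5, 2, 0) gives 2 of 9. Monday/Tuesday/Sunday (g = 6, 5, 0) gives 1 of 9.

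Session 9 fails on every calendar, because it has at most 10 days.

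**Shorter limits.** Session 9 is still followed for 7 to 10 days, against limits of 3 days and 60/24 = 2.5 days. These limits can be observed after all nine sessions.

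**The case against.** The strongest reply is that nothing is lost. The general definition has no duration or causality limit, events are collected at every visit in both arms, and a randomised comparison of all adverse events needs no relatedness label. That stands for total recorded harm. A reader might infer that the trial understates harm overall, and the documents do not support that. The reply does not rescue the related count, because a short event recorded under the general definition is still outside the acupuncture-related category.

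Other strong readings also fail:
- That related events count only above long durations: dizziness and palpitation have no limit, and the lists are introduced as non-exhaustive. That openness does not lift the limits on the symptoms named with one.
- That late sessions can yield no related event: only the two-week item meets the observation limit.
- That most ordinary needling harms are excluded: the documents give no distribution of event types or durations.

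It can also be said that the article does not state that observation of an unresolved event stops at visit 11, and that the full protocol may provide for longer follow-up. This is fair. The conflict is therefore with the last scheduled assessment, and the silence on later follow-up is not itself a fault.

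**Conclusion.** The point holds in a limited form. For several named local and psychiatric symptoms the article fixes relatedness by duration, which biases the acupuncture-related count downward. The size of that bias cannot be computed from the documents.

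The two-week item also cannot be confirmed at the last scheduled safety visit for the latest sessions: 3 or 4 of 9 on an assumed Monday/Wednesday/Friday calendar, and 1 or 2 of 9 on some weekend calendars with visit 11 at 10 days. It is never none. These are shares of sessions, not of events. The primary outcome is unaffected. What is weakened is one safety summary under a stated aim, so the text should be changed before related-event rates are reported.

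**What to change.** Reconcile the Adverse events section with Table 1:
- Judge relatedness to needling separately from duration.
- Report, by arm, all adverse events and all needling-related events regardless of duration.
- Keep the present cut-offs only to label a longer-lasting subset, and state whether the two-week cut-off covers bruising as well as pain.
- Count events unresolved at visit 11 as ongoing, so that a late event is not treated as having failed the two-week criterion.

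The cost is a change of wording and, if the form lacks them, start and stop dates. Safety is already assessed at visits 2 to 11, so no visit is added. The small downside is more minor events to list.

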### Ethics

Written consent will be obtained from each participant. This study protocol was approved by the institutional review board of Daejeon University hospital.

## Abbreviations

ANCOVA: analysis of covariance; CAM: complementary and alternative medicine; CRC: clinical trial coordinators; KIOM: Korea Institute of Oriental Medicine; MQS: Medication Quantification Scale; OSDI: Ocular surface disease index; RCTs: randomised controlled trials; SD: standard deviation; TFBUT: Tear Film Break-Up Time; VAS; Visual analogue scale.

## Appendix 1. Inclusion and Exclusion Criteria

### Inclusion Criteria

Patients who have had dry eye syndrome in a single eye or in both eyes (ICD-10: H04.1).

He or she must have both of the conditions below:

• Patients who have been having symptoms such as ocular itching, ocular foreign body sensation, ocular burning, ocular pain, ocular dryness, blurred vision, sensation of photophobia, ocular redness or sensation of tearing

• Patients whose Tear Film Break-Up Time (TFBUT) is below 10 seconds and measured tear amount is below 10 mm/5 sec by the Schirmer I test

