### Inclusion and exclusion criteria

Eligible participants of both sexes who have moderate to severe levels of dry eye will be enrolled according to the inclusion and exclusion criteria. In addition to abnormal ophthalmological test results (Tear Film Break-Up Time and Schirmer I test), they must have symptoms of dry eye such as ocular itching, ocular foreign body sensation, ocular pain, ocular dryness, or vision problems, which may include blurred vision or a sensation of photophobia. Special medical conditions and conditions that can increase adverse event risk or might be expected to mislead interpretation of the outcome after acupuncture treatment comprise the exclusion criteria (Appendix 1).

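### The Schirmer I entry threshold is written per 5 seconds, but the test it refers to runs five minutes; taken literally, this one component would exclude practically nobody

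*Protocol article*

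**What the plan says.** Under Inclusion Criteria, Appendix 1 of the protocol article requires symptoms and, in a second bullet, two test results together. The first is "Patients whose Tear Film Break-Up Time (TFBUT) is below 10 seconds". The second is that the "measured tear amount is below 10 mm/5 sec by the Schirmer I test".

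The section Secondary outcome measurement describes how the Schirmer I test is done: the paper is placed on the lateral third of the "lower eyelid with the participant's eye closed for five minutes". Table 1 schedules the test at visit 1 (screening) and at visit 10 only.

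The section Inclusion and exclusion criteria states what the tests are for at entry: "In addition to abnormal ophthalmological test results (Tear Film Break-Up Time and Schirmer I test), they must have symptoms of dry eye".

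**The concern.** An entry threshold works only if it is on the scale of the measurement it is compared with. Here the limit is a wetting length per 5 seconds, while the only procedure described gives a wetting length after five minutes. It is also one of just two numerical entry limits; the symptom criterion carries no score.

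Read literally, the limit is so loose that people with ample tear secretion would meet it. The Schirmer part of the entry rule would then do no work, contrary to the stated requirement for an abnormal result. Because Table 1 has no Schirmer measurement between screening and visit 10, the screening value is also the only pre-treatment value for the secondary Schirmer outcome. Admitting people with normal secretion would leave less room for improvement on it.

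**Working it through.** The plan gives no calculated figure to reproduce. The check is a unit conversion, followed by a test of whether the conclusion depends on how wetting progresses.

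**Inputs**
- Threshold as written: 10 mm per 5 s (Appendix 1).
- Test duration: five minutes = 300 s (Secondary outcome measurement).
- Wetting reached in five minutes: not given in the document. A range of 10 to 50 mm is assumed here.

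**Step 1: ratio of the time bases.** 300 s / 5 s = 60.

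**Step 2: written threshold on the five-minute scale, constant rate.** 10 mm × 60 = 600 mm per five-minute test.

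**Step 3: a 10 mm, five-minute result on the 5-second scale, constant rate.** 10 mm / 60 = 0.17 mm in 5 s.

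**Step 4: drop the constant-rate assumption.** Let wetting be front-loaded, in proportion to the square root of time. The share of the five-minute wetting reached in the first 5 s is then √(5/300) = 0.129, against 5/300 = 0.0167 at a constant rate.

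| Assumed wetting in 5 min (mm) | First 5 s, constant rate (mm) | First 5 s, front-loaded (mm) |
|---|---|---|
| 10 | 0.17 | 1.3 |
| 15 | 0.25 | 1.9 |
| 20 | 0.33 | 2.6 |
| 35 | 0.58 | 4.5 |
| 50 | 0.83 | 6.5 |

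Every entry is below 10 mm, so every such person would pass the written limit.

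**Step 5: five-minute wetting needed to fail the written limit.** Constant rate: 10 / 0.0167 = 600 mm. Front-loaded: 10 / 0.129 = about 77 mm.

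Under either pattern, and across the whole assumed range, the Schirmer limit as written does not bind.

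**The case against.** The strongest reply is that the document itself points to the intended reading. It describes one Schirmer procedure, lasting five minutes, performed by a single ophthalmologist. Physicians and ophthalmologists examine eligibility, and the text asks for an abnormal result. A screener who follows the procedure obtains a five-minute value; literal use of the limit would need a 5-second reading that is described nowhere. Seconds written for minutes is the natural explanation. This stands, and it means that the practical effect may be small. It does not remove the contradiction in a threshold that decides who is randomised.

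A reader might go further in four ways that the document does not support:

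- *That the entry criteria as a whole admit almost anyone.* They do not. The Schirmer limit is joined by an and to TFBUT below 10 seconds. Symptoms and a dry eye diagnosis are also required, and Appendix 1 lists 13 exclusion criteria.
- *That people with normal secretion will be enrolled.* This follows only if staff apply the unit literally, against the described procedure.
- *That the slip makes the description of the population as moderate to severe untrue.* The article says that such patients are enrolled under the criteria; it nowhere says that these two limits define severity. Whether the label needs a symptom cut-off is a separate question, and so is whether both tests must be met in the same eye, a detail that a condensed article may leave to the full protocol.
- *That the primary result is compromised.* The primary outcome is the Ocular Surface Disease Index, a questionnaire score. Schirmer is one of several secondary outcomes, and nothing in the document allows an effect on the primary comparison to be sized.

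**Conclusion.** The point holds as an internal contradiction in an operative eligibility threshold. Appendix 1 and the Secondary outcome measurement section disagree on the time base of the Schirmer I test by a factor of 60. Taken literally, the Schirmer component would exclude practically nobody: failing it would need between about 77 mm (front-loaded) and 600 mm (constant rate) of wetting in five minutes.

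The factor of 60 comes directly from the document. The 77 to 600 mm range rests on the two assumed wetting patterns, and calling the limit non-binding rests on the assumed 10 to 50 mm range, since the article gives no distribution of wetting and no strip length. Any dilution of the population or of the secondary Schirmer outcome is conditional on literal use, which the described procedure makes unlikely. The line should be corrected; it is not a ground for doubting the trial as a whole.

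**What to change.** Reconcile the time unit of the Schirmer threshold in Appendix 1 with the test duration in Secondary outcome measurement, so that the limit and the reading share one time base. Check that any screening form or eligibility checklist carries the same unit. The cost is one unit in one line, plus the form check. The sample size, visit schedule and analysis are unaffected.
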